### Phase I part of PANDORA-01

It is the aim of the Phase I part of this study to determine the MTD for carbon ion radiotherapy for the treatment of recurrent rectal cancer. The primary endpoint is the occurrence of a dose limiting toxicity defined as any Grade IV toxicity according to CTCAE Version 4.0, possibly, probably or definitely associated to study treatment and occurring during 30 days after completion of the study treatment.

The calculation of the sample size for the Phase I part of the PANDORA-01 trial is based on the traditional 3 + 3 dose escalation scheme which is conducted as follows:

Patients are treated in cohorts of three each receiving the same dose. For the assessment of a dose limiting toxicity (see definition above) patients are observed for 30 days after application of the study treatment.

If none of the three patients of a cohort exhibits a dose limiting toxicity, the next cohort of three patients receives the next higher dose.

Otherwise, if at least one patient of a cohort exhibits a dose limiting toxicity, a further cohort of three patients is treated at the same dose level without escalating the dose.

If exactly one out of the six patients treated at this dose exhibits a dose limiting toxicity, the trial continues as planned at the next higher dose level.

If two or more patients out of the six patients treated at this dose exhibit a dose limiting toxicity, the dose escalation stops at that level and the next lower dose is considered as the MTD. When the escalation has stopped, additional patients will be treated at the MTD to a total of nine patients.

The Phase I part of the trial is conducted to determine the MTD of carbon ion radiotherapy by consideration of a total of seven dose levels. Therefore, the maximum sample size is 45 patients (six dose levels with a maximum of 6 patients each and 9 patients at the MTD).

Primary endpoint to determine the MTD that is chosen out of seven dose levels is any Grade IV toxicity according to CTCAE Version 4.0, possibly, probably or definitely associated to study treatment and occurring during 30 days after completion of the study treatment. Secondary endpoints are other safety data on the applied dose levels as well as response, progression-free survival, and overall survival.

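### The written 3 + 3 rule treats three more patients at a dose after 2 or 3 DLTs in the first three, when stopping is already certain

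*Protocol article*

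**What the plan says.** The section on the Phase I part within the statistical considerations says that the sample size is "based on the traditional 3 + 3 dose escalation scheme which is conducted as follows", and then sets out these steps:

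- No DLT in three: "If none of the three patients of a cohort exhibits a dose limiting toxicity, the next cohort of three patients receives the next higher dose".
- Every other result, that is, whenever "at least one patient of a cohort exhibits a dose limiting toxicity, a further cohort of three patients is treated"; these extra patients stay on the unchanged dose.
- One DLT in six: "If exactly one out of the six patients treated at this dose exhibits a dose limiting toxicity, the trial continues as planned", one step up.
- Two or more in six: "If two or more patients out of the six patients treated at this dose exhibit a dose limiting toxicity, the dose escalation stops", and the dose below becomes the MTD, which is then filled to nine patients.

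A DLT is a Grade IV event (CTCAE 4.0) at least possibly related to treatment, up to 30 days after treatment ends. The Background also calls the design a classical 3 + 3. No sentence in the article stops a level on the strength of the first three patients alone. The data safety monitoring board section provides for at least two reviews a year and states no rule at cohort level.

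**The concern.** The expansion trigger is one or more DLTs in three, and the stop criterion is two or more in six. When the first three patients already show two or three DLTs, the stop criterion is bound to be met, so the second cohort has no bearing on the decision. The usual 3 + 3 scheme, which the article names, expands only on exactly one DLT in three and stops at two or more. The written rule departs from it without giving a reason.

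The stake is patient safety. A DLT here is a Grade IV event, and every patient has had 20 to 60 Gy of photon irradiation before. Followed literally, the rule would give three more such patients a dose that has just produced Grade IV toxicity in two or three of three, for no gain in the dose decision.

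**Working it through.** **Inputs from the article.** Cohorts of three; the four rules above; seven dose levels; stated Phase I maximum of 45. The article gives no DLT rate, so the true rate p is an assumption, shown over a range.

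**The plan's own figure.** Six levels × 6 patients + 9 at the MTD = 36 + 9 = 45. This reproduces.

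**Is the second cohort ever informative after 2/3 or 3/3?** Let a be the DLTs in the first cohort and c those in the second.

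- a = 2, c = 0, 1, 2, 3 gives totals 2, 3, 4, 5.
- a = 3, c = 0, 1, 2, 3 gives totals 3, 4, 5, 6.

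All eight totals are at least 2, so escalation stops in every case. By contrast, a = 1 with c = 0 gives 1 of 6 (escalate) and a = 1 with c ≥ 1 gives at least 2 of 6 (stop). Only after exactly one DLT can the second cohort change the decision.

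**How often this state arises at one level.** With X ~ Bin(3, p):

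- P(X ≥ 2) = 3p²(1 − p) + p³.
- Share of second cohorts opened with the stop already certain = P(X ≥ 2) / [1 − (1 − p)³].
- Expected further DLTs in such a cohort = 3p.

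| p | P(X ≥ 2) | Share of second cohorts | Further DLTs, given that it happens |
|---|---|---|---|
| 0.05 | 0.007 | 5% | 0.15 |
| 0.10 | 0.028 | 10% | 0.3 |
| 0.20 | 0.104 | 21% | 0.6 |
| 0.30 | 0.216 | 33% | 0.9 |
| 0.40 | 0.352 | 45% | 1.2 |
| 0.50 | 0.500 | 57% | 1.5 |

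Example at p = 0.3: 3 × 0.09 × 0.7 + 0.027 = 0.189 + 0.027 = 0.216; and 0.216 / (1 − 0.343) = 0.33.

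**Over a whole trial.** A level is passed with probability (1 − p)³ + 3p(1 − p)² × (1 − p)³. Multiplying the pass probabilities up to each level by P(X ≥ 2) at that level, and summing over the seven levels, gives the chance that a trial opens such a cohort. Every curve below is an assumption.

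| Assumed DLT rates, levels 1 to 7 | Trials opening such a cohort |
|---|---|
| 0.05, 0.08, 0.12, 0.17, 0.23, 0.30, 0.38 | 35% |
| 0.02, 0.03, 0.05, 0.07, 0.10, 0.13, 0.17 | 14% |
| 0.01, 0.02, 0.03, 0.04, 0.06, 0.08, 0.10 | 6% |
| 0.05 at every level | 5% |

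On the steepest curve, the expected number of extra DLTs per trial, averaged over all trials, is about 0.26.

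**Effect of correcting the rule.** Expand on exactly 1/3 and stop on 2/3 or 3/3.

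- Decisions: the escalate and stop probabilities at a level are identical under both rules (at p = 1/3, 0.428 and 0.572).
- Expected patients at a level: 3 + 3[1 − (1 − p)³] as written, against 3 + 3 × 3p(1 − p)² corrected. That is 4.46 against 4.15 at p = 0.2, 5.35 against 4.30 at p = 0.4, and 5.63 against 4.13 at p = 0.5.
- Maximum: still 45, because six patients per level remain possible through 1/3.

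**Time.** With five fractions a week, and all three patients starting together (both assumed), a further cohort takes 12/5 × 7 + 30 = 46.8 days at the lowest dose and 18/5 × 7 + 30 = 55.2 days at the highest. The whole cohort could fall between two half-yearly board reviews.

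**The case against.** The strongest reply is that this is loose wording in a condensed article. It names the "traditional 3 + 3 dose escalation scheme", so the standard rule was probably meant, and investigators would stop after two Grade IV events in three patients. That may well be so. But the text sets out the conduct step by step and the trigger is explicit. This is not a detail left to another document, and a dose rule has to be safe when followed as written.

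Four further points stand and limit the size of the problem:

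- No inference changes. MTD selection, the escalation probabilities and the maximum of 45 are the same either way.
- It can occur at most once per trial, because escalation ends at that level, so at most three patients are affected.
- The DLT definition is narrow (related, Grade IV, within 30 days of completion), so low rates are plausible. The whole-trial chance runs from about 5% to 35% over the assumed curves, and no single figure should be relied on.
- The stop rule is worded on six patients, so after 2/3 or 3/3 it is certain to be met but not yet formally met.

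The monitoring board can recommend termination, which is a partial safeguard. At two reviews a year as the stated minimum, it does not replace a cohort rule.

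**Conclusion.** The concern holds. As written, the expansion step enrols patients 4 to 6 at a dose whose rejection is already settled, and it contradicts the scheme that the article names. That conclusion is purely logical and needs no assumed rate. The size does depend on the unknown DLT rate: P(X ≥ 2) at a level runs from under 1% at 0.05 to 50% at 0.5. The harm is avoidable exposure of up to three patients to Grade IV toxicity, with no effect on the statistical conclusions. Because it is an explicit dosing rule with a safety consequence, it must be corrected before patients are treated under it.

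**What to change.** Change the trigger for the second cohort to exactly one DLT among the first three patients at a level. Add a sentence: if two or more of the first three have a DLT, escalation stops without further enrolment at that dose, and the next lower dose is taken as the MTD. Leave the rules for six patients as they are.

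The cost is one amended sentence and one added. The maximum stays at 45, the escalation decisions are identical, and the number of patients treated can only fall.

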### Phase II part of PANDORA-01

The primary objective of the Phase II part of PANDORA-01 is to evaluate the 12 month progression-free survival rate *π *for patients with recurrent rectal cancer receiving carbon ion radiotherapy. According to results reported in the literature, the 12 month progression-free survival rate for patients treated with conventional radiotherapy is estimated to be 0.60. Thus, the confirmatory analysis of the primary endpoint assesses the following test problem: *H*_0_: *π *≤ 0.60 = *π*_0 _versus *H*_1_: *π *> 0.60.

The sample size calculation for the confirmatory analysis of the Phase II part of the study refers to the test problem given above that will be assessed applying a one-sided binomial test at an overall type I error rate of *α *= 0.05. A power of 1-*β *= 0.80 is aspired for the alternative of a 12 month progression-free survival rate of *π*_1 _= 0.80, i.e., for an absolute improvement of 0.20 as compared to conventional radiotherapy. As this Phase II part of PANDORA-01 is the first study providing data on the efficiency of carbon ion therapy for the treatment of recurrent rectal cancer, there is considerable uncertainty with respect to the actual 12 month progression-free survival rate resulting from carbon ion therapy in this patient population: The rate may be higher than 0.80 thus requiring fewer patients for the study; or it may be slightly lower than 0.80 while the improvement may still be clinically relevant, but with the consequence for the study that more patients than initially planned would be required to assure the desired power. For this reason, an adaptive version of Simon's optimal two-stage design is used for this Phase II study part [23,24]. This design enables to change the initially specified sample size based on the results of a planned interim analysis. If the sample size is not modified, a maximum total of 39 patients is included, with an interim analysis after *n*_1 _= 14 patients and further *n*_1 _= 25 patients recruited for the second stage if the study is continued after stage 1. Using the decision rules given, this design assures the desired power 1- *β *= 0.80 for the alternative *π*_1 _= 0.80 and has an expected sample size of 20.8 under the null hypothesis *π*_0 _= 0.60. According to the design of the Phase I part of PANDORA-01, 9 patients are already treated there with the MTD.

The primary outcome variable is the 12 month progression-free survival rate. Secondary objectives are the assessment of the 12 month overall survival rate as well as safety and tolerability.

More details on the statistical analysis will be provided in the statistical analysis plan which is finalized prior to performing any analysis and which has to be authorized by the study biostatistician and the principal investigator.

### Data safety monitoring board (DSMB)

An independent Data and Safety Monitoring Board (DSMB) will monitor the recruitment, the reported adverse events and the data quality at least twice a year. Based on its review the DSMB will provide the Principal Investigator (PI) with recommendations regarding trial modification, continuation or termination.

### Data collection and management

According to the §13 of the German GCP-Regulation all important trial documents will be archived for at least 10 years after the end of the PANDORA-01 trial. According to the §28c of the German X-Ray Regulation (RöV) and the §87 of the German Radiation Protection Regulation (StrlSchV) the informed consent forms including patients' consent for trial participation, application of irradiation and data transmission to the competent authority will be archived for at least 30 years after the end of the trial. The Study Center at the Deparment of Radiation Oncology Define will be responsible for archiving allrelevant data.

### Ethical and legal aspects

*The protocol will be condected according the guidelindes of *Good Clinical Practice (GCP) and the ethical principles described in the Declaration of Helsinki (2008 Version of the Declaration of Helsinki, adopted at the 59th WMA General Assembly, Seoul, October 2008).

The trial will be carried out by adhereing to local legal and regulatory requirements.

The study plan has obtained approval by the Institutional Review Board (IRB)/Independent Ethics Committee (EC) of the Medical Faculty Heidelberg. Before start of recruitment a positive vote of the Bundesamt für Strahlenschutz (BfS) is necessary.

## Discussion

The aim of the present PANDORA-01 trial is to evaluate the MTD for carbon ion radiotherapy in patients with recurrent rectal cancer, previously treated with radiation; subsequently, the efficacy of carbon ion radiotherapy will be evaluated in the Phase II part of the study.

To date, the possibility to treat patients with inoperable recurrent rectal cancer with radiation as a second course of radiotherapy had proven only modest effectivity, with a potential risk of treatment-related side effects [14,15,25,26]. However, the physical and biological characteristics of the carbon ion beam potentially offer a treatment alternative in this clinical situation. Previous studies from Japan on carbon ion radiotherapy for rectal cancer have shown promising results [21,27-29]. However, the published data focus on carbon ion radiotherapy applied in radiation-naïve patients. In Europe, the majority of patients presenting with recurrent rectal cancer have been treated with radiation during first-line treatment, either with preoperative chemo-radiation, short-term regimens, such as 5 × 5Gy, or with adjuvant chemoradiation, depending on tumor stage and institutional preferences.

Taking all these aspects into consideration, the present trial was designed as a Phase I/II trial firstly evaluating the MTD for carbon ion radiotherapy, followed by evaluation of efficacy in the Phase II part of the trial.

Carbon ion radiotherapy will be applied using the rasterscanning technique. A typical treatment plan can be observed in Figure 1. Patients will be followed closely to document all treatment-related side effects, as well as to assess treatment response and tumor control.

**Figure 1 F1:**
[figure not shown]
**Typical treatment plan for carbon ion radiotherapy applied with the rasterscanning technique in a patients with locally recurrent rectal cancer axial sagittal and coronal view**.

In conclusion, the PANDORA-01 study is the first trial to evaluation high-LET particle therapy with carbon ions as re-irradiation in patients with locally recurrent and unresectable rectal cancer.

## Abbreviations

ACC: Adenoid Cystic Carcinomas; BDSG: Bundesdatenschutzgesetz; CEA: Carcino-Embryonal Antigen; CHT: Chemotherapy; CRF: Case Report Form; CRP: C Reactive Protein; CT: Computer tomography; CTCAE: Common Toxicity Criteria for Adverse Events; CTV: Clinical target volume; DKFZ: Deutsches Krebsforschungszentrum; DRR: Digitally reconstructed radiograph; DVH: Dose volume histogram; GCP: Good Clinical Practice; GSI: Gesellschaft für Schwerionenforschung; GTV: Gross tumor volume; Gy: Gray; Gy E: Cobalt Gray equivalent; ICD: International Classification of Disease; LET: Linear energy transfer; LLUMC: Loma Linda University Medical Center; MGH: Massachusetts General Hospital; MR: Minor responses; MRI: Magnet resonance imaging; MTD: Maximal Tolerable Dose; n.a.: Not applicable; NIRS: National Institute of Radiological Sciences; OS: Overall survival; PR: Partial response; PTV: Planning target volume; RBE: Relative biological effectiveness; SD: Stable disease; RT: Radiation therapy; SAE: Severe Adverse Events; TME: Total Mesorectal Excision.
